Previous trials of CEA versus medical therapy assessed only clinically manifest stroke reported by the patient and confirmed by adjudication in line with the definition of stroke as symptoms likely to be of cerebrovascular origin lasting at least 24 h. However, brain magnetic resonance imaging (MRI) is much more sensitive than clinical assessment in detecting ischaemic brain infarcts. Silent brain infarcts on MRI were found in 8% of participants in the Rotterdam study [12] and developed in 20% of participants after 10 years of follow-up in the Atherosclerosis Risk in Communities Brain Magnetic Resonance Imaging Study [13]. Silent infarcts on MRI are also seen after revascularisation procedures [14–17]. MRI can detect cerebral infarcts in the absence of clinical signs and symptoms and approximately doubles the number of episodes of cerebral infarction (clinically manifest and silent stroke) detected during follow-up. Thus, incorporation of new infarcts on brain MRI as an outcome measure is more sensitive than clinical assessment and therefore reduces the sample size required to demonstrate significant differences in the outcome between the two treatments. Another advantage of using MRI to assess outcome after stroke is that the determination of outcome is more objective than clinical assessment and outcome assessment can be done independently and blind to treatment and patient characteristics, unlike clinical assessment.

Furthermore, MRI is able to detect structural features of plaque instability, such as intra-plaque haemorrhage (IPH), which may improve the identification of patients benefitting from carotid revascularisation. The presence of IPH increases the risk of stroke in patients with carotid stenosis by a factor of more than ten and predicts risk independently of the degree of stenosis [18].

These considerations argued for a new trial to investigate the role of revascularisation in the setting of improved medical therapy adjusted to targets for risk factor control, i.e. optimised medical therapy (OMT), and using brain MRI to determine outcome measures. We therefore organised the Second European Carotid Surgery Trial (ECST-2).

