### Sample size {14}

We expect a rate of stroke in the OMT arm of approximately 3% at 2 years after randomisation. Silent ischaemic infarcts on MRI seem to occur at twice the frequency of clinically manifest strokes [42, 43]. Thus, we expect about 9% of patients on OMT to experience clinically manifest stroke or have silent new ischaemic infarct on MRI after 2 years of follow-up. In those allocated to revascularisation, we expect a peri-operative risk of stroke of 3% and a subsequent 2-year risk of stroke of 2%. Thus, we expect about 15% of patients in the revascularisation arm to experience clinically manifest stroke or have silent new ischaemic infarct on MRI after 2 years of follow-up.

The rate of clinically manifest periprocedural myocardial infarction (MI) in carotid revascularisation is about 1% [44]. The 2-year risk of non-periprocedural MI is expected to be about 2% using the Framingham model [45] based on the characteristics of patients in the International Carotid Stenting Study (ICSS) [46]. We therefore estimated a total 2-year risk of MI of 3% in patients randomised to revascularisation and 2% in those randomised to OMT. The periprocedural death rate (unrelated to MI or stroke) in ICSS patients undergoing CEA was 0.1%. The rate of the primary outcome event in ECST-2 of clinically manifest stroke, new ischaemic infarct on MRI, MI or periprocedural death at 2 years was therefore estimated at 11% in the OMT arm alone and 18% in the revascularisation arm. Assuming these outcome event rates, 314 patients (157 in each arm) provide 80% power to demonstrate that OMT is non-inferior to OMT plus revascularisation with a non-inferiority margin of 4%. Allowing for a dropout of 15% of patients missing their 2-year MRI, we plan to recruit 360 patients for the MRI-based analysis.

We originally calculated a sample size of 2000 patients for the full ECST-2 trial, details of which can be found in the trial protocol. The sample size calculation for the continuation or re-launch of the study will be based on the outcome rates determined in the initial analysis.

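### The 11% and 18% composite rates are plain sums of component risks and use an infarct ratio that differs from the Background, so the stated 80% power is conditional and has no reserve

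*Protocol article*

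**What the plan says.** All the planning inputs are in the protocol article under Sample size {14}.

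- **OMT arm.** The starting point is clinical stroke: "We expect a rate of stroke in the OMT arm of approximately 3% at 2 years after randomisation". Silent infarction is then added: "Silent ischaemic infarcts on MRI seem to occur at twice the frequency of clinically manifest strokes". The result is that "we expect about 9% of patients on OMT to experience clinically manifest stroke or have silent new ischaemic infarct on MRI".
- **Revascularisation arm.** Stroke risk is 3% peri-operatively plus 2% afterwards. The same multiplier leads to the statement that "we expect about 15% of patients in the revascularisation arm to experience clinically manifest stroke or have silent new ischaemic infarct on MRI".
- **MI and death.** The 2-year MI risk is 2% on OMT and 3% with revascularisation. Periprocedural death not due to MI or stroke is 0.1%.
- **Composite.** The primary outcome rate is "estimated at 11% in the OMT arm alone and 18% in the revascularisation arm". With a 4% non-inferiority margin, "314 patients (157 in each arm) provide 80% power".

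Background and rationale {6a} describes the yield of MRI differently. There, MRI "approximately doubles the number of episodes of cerebral infarction (clinically manifest and silent stroke) detected during follow-up".

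**The concern.** The primary outcome of the initial analysis counts patients with at least one of stroke, new infarct on MRI, MI or periprocedural death. A patient with a stroke and an MI counts once. Adding the component risks gives the composite rate only if no patient has two components. The article neither states nor justifies that assumption, and it moves from a frequency of silent infarcts to a percentage of patients without comment.

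The multiplier is a second, separate matter. The sample size section sets silent infarcts at 2 x clinical stroke, so total infarction is 3 x clinical stroke. The Background says that clinical and silent episodes together are about 2 x the clinical number.

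Both choices feed the assumed 7-point advantage of OMT. That advantage plus the 4-point margin is what generates the 80% power. A reader of an inconclusive non-inferiority result needs to know how far that figure depends on these two choices.

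**Working it through.** **Formula.** With pO and pR the composite rates on OMT and revascularisation, margin 0.04, n per arm, unpooled variance and one-sided 2.5%:

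power = Φ[ (pR − pO + 0.04) / √{(pO(1 − pO) + pR(1 − pR)) / n} − 1.96 ]

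n for 80% = (1.96 + 0.842)² × (pO(1 − pO) + pR(1 − pR)) / (pR − pO + 0.04)²

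The article does not state alpha. One-sided 2.5% is inferred because it reproduces the stated size. One-sided 5% gives 126 per arm for 11% against 18% and does not.

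**Step 1: reproduce the plan.**
- OMT: 3 + (2 × 3) + 2 = 11%.
- Revascularisation: (3 + 2) + (2 × 5) + 3 + 0.1 = 18.1%, printed as 18%.
- Variance term: 0.11 × 0.89 + 0.181 × 0.819 = 0.2461. Standard error: √(0.2461/157) = 0.0396.
- Power: Φ(0.111/0.0396 − 1.96) = Φ(0.843) = 80.05%. The n for 80% is 156.8, that is 157 per arm.
- With the printed 18%, power at 157 is 79.4% and 160 per arm are needed.

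The unrounded sum therefore gives the published sample size exactly.

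**Step 2: allow for overlap (the overlap pattern is an assumption).**
- *Only MI overlaps, independently.* OMT 1 − 0.91 × 0.98 = 10.8%. Revascularisation 1 − 0.85 × 0.97 × 0.999 = 17.6%.
- *Stroke, silent infarct, MI and death all independent.* OMT 1 − 0.97 × 0.94 × 0.98 = 10.6%. Revascularisation 1 − 0.95 × 0.90 × 0.97 × 0.999 = 17.1%.
- *As above, with peri-operative and later risks also independent.* OMT 10.6%. Revascularisation 1 − 0.97 × 0.98 × 0.94 × 0.96 × 0.99 × 0.98 × 0.999 = 16.9%.

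**Step 3: use the Background ratio and keep plain sums.**
- OMT: 2 × 3 + 2 = 8%.
- Revascularisation: 2 × 5 + 3 + 0.1 = 13.1%.

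| Assumption | OMT | Revasc. | Difference (points) | Power at 157 | n per arm for 80% |
|---|---|---|---|---|---|
| Plain sums | 11.0% | 18.1% | 7.1 | 80.05% | 157 |
| MI independent only | 10.8% | 17.6% | 6.8 | 78.7% | 163 |
| All components independent | 10.6% | 17.1% | 6.5 | 77.1% | 169 |
| Independent, periods also split | 10.6% | 16.9% | 6.2 | 75.1% | 178 |
| Background ratio, plain sums | 8.0% | 13.1% | 5.1 | 75.0% | 178 |

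**Step 4: test whether overlap must lower power.**
- One point removed from both arms (10% / 17.1%): the difference stays at 7.1 points, the variance falls, and power is 82.4%.
- One point removed from OMT only (10% / 18.1%): 87.4%.
- One and a half points removed from revascularisation only (11% / 16.6%): 69.7%.

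The direction depends on how overlap is distributed between the arms, and the article gives no figure for that.

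**The case against.** Four points can be made for the plan.

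First, the largest overlap may not exist. If silent infarct means a new infarct in a patient without clinical stroke, then 3 + 6 and 5 + 10 are sums of disjoint groups and are correct. The death term is already defined as unrelated to MI or stroke. Only MI could then overlap, and under independence that costs 1.3 points of power. The article does not settle the meaning, so this stands as a possible reading. It does not touch the conflict over the ratio.

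Second, the shift is small beside the roughness of the inputs. Rounding 18.1% to 18% alone moves power to 79.4%, and a Farrington-Manning variance at 11% / 18% gives 78.3%. This is fair, and it is why the point concerns how the power is stated and not whether the design is sound.

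Third, the Discussion concedes that event rates may differ from those predicted, and the sample size section bases the re-launch on observed rates. The planning sums will therefore not be carried forward, and nothing needs changing there. The general caveat does not say how the present rates were built.

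Fourth, a reader might infer that 80% is an upper limit because a sum is the largest value a composite rate can take. The documents do not support that. The sum bounds each rate, but not their difference or the power. Step 4 of the working shows equal absolute overlap, or overlap mainly on OMT, raising power above 80%.

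**Conclusion.** The point holds in a limited form. The composite rates are plain sums with no stated allowance for patients with several components, and the infarct multiplier contradicts the Background. The stated 80% has no reserve and is conditional on both choices.

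At 157 per arm and an inferred one-sided 2.5%, independence gives 78.7% (MI only) or 77.1% (all components), with 75.1% under the finest split. The Background ratio alone gives 75.0% and needs no overlap assumption. The range of about 75% to 80% changes one choice at a time. It is not a bound in either direction, because overlap concentrated in one arm can move power outside it.

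A reader might also take one of the lower figures as the true or more realistic power. The documents give no overlap fraction, so independence is as much an assumption as disjoint events. The size of the effect, up to about 5 points, warrants a correction of the text. It does not show that the initial analysis is invalid.

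**What to change.** In the sample size section:

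1. Reconcile the silent-to-clinical infarct ratio with the statement in Background and rationale {6a}. Say which ratio is used and whether it counts episodes or patients.
2. State the overlap assumption behind 11% and 18%, including whether silent infarct excludes patients with clinical stroke.
3. State the alpha used, and give the power of 157 per arm as conditional, with a range of about 75% to 80% under the assumptions tabulated above.

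The cost is one paragraph and a slightly less favourable stated power. No patients are added, and the re-launch calculation needs no change.

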### Objectives {7}

The objective of ECST-2 is to investigate the hypothesis that patients with carotid stenosis ≥50% associated with a low to intermediate risk of stroke will not benefit from additional carotid revascularisation when treated with optimised medical therapy. We also aim to investigate the hypothesis that the findings on baseline carotid plaque imaging can be used to predict future stroke risk and identify a subgroup of patients that will benefit from carotid revascularisation.

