### Trial design {8}

ECST-2 is designed as a multicentre, prospective, randomised, controlled, open, multi-centre, non-inferiority clinical trial with blinded outcome adjudication of the primary outcome and 1:1 allocation to the two treatment arms balanced by minimisation.

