## Discussion

The objective of ECST-2 is to test the hypothesis that patients with carotid stenosis ≥50% associated with a low to intermediate risk of stroke will not benefit from additional carotid revascularisation when treated with optimised medical therapy, because vascularisation surgery will cause more periprocedural vascular events than are prevented by removal of the plaque. ECST-2 is designed to closely reflect current medical practice so that the results of the trial are applicable to everyday medicine.

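### The 4-point non-inferiority margin is wider than the 3-point gross preventive effect implied by the plan's own rates, so a pass does not by itself establish that patients will not benefit from revascularisation

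*Protocol article*

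**What the plan says.** Trial design {8} describes a "non-inferiority clinical trial with blinded outcome adjudication of the primary outcome and 1:1 allocation to the two treatment arms". Objectives {7} gives the hypothesis: patients with carotid stenosis at low to intermediate risk "will not benefit from additional carotid revascularisation when treated with optimised medical therapy". The Discussion adds the mechanism: "because vascularisation surgery will cause more periprocedural vascular events than are prevented by removal of the plaque".

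Sample size {14} builds the 2-year composite of clinical stroke, new infarct on MRI, myocardial infarction (MI) or periprocedural death from its parts. For OMT: "We expect a rate of stroke in the OMT arm of approximately 3% at 2 years after randomisation". For the other arm: "we expect a peri-operative risk of stroke of 3% and a subsequent 2-year risk of stroke of 2"%. Silent infarcts are taken to be twice as frequent as clinical strokes, which gives 9% and 15% for stroke or infarct. MI is put at 2% on OMT and at 3% with revascularisation, where 1 point is periprocedural. Periprocedural death is put at 0.1%. The composite is then "estimated at 11% in the OMT arm alone and 18% in the revascularisation arm", and "80% power to demonstrate that OMT is non-inferior to OMT plus revascularisation with a non-inferiority margin of 4"%.

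The article states neither the basis of the margin nor the significance level.

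**The concern.** The hypothesis in Objectives {7} and the Discussion says that the event rate on OMT is no higher than with revascularisation: a difference, OMT minus revascularisation, of zero or below. The only pass mark in the article is a difference below 4 points. A margin is normally judged against the effect that might be given up. Here that is the long-term prevention attributed to the procedure.

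If the margin exceeds the whole of that effect, meeting it leaves open whether any benefit exists. The quoted 80% power would then apply to a weaker statement than the hypothesis. The results are also to inform a re-launch, and Trial status allows that its design may be similar, so the margin could be carried into a much larger trial.

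**Working it through.** **Inputs.** All rates, the margin and 157 per arm come from Sample size {14}. One-sided 2.5% is assumed.

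**1. The plan's own figure.** With rates 11% and 18%, the variance sum is 0.11 × 0.89 + 0.18 × 0.82 = 0.0979 + 0.1476 = 0.2455. The distance from the margin is 4 + 7 = 11 points.

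- One-sided 2.5%, 80% power: n = 0.2455 × (1.960 + 0.842)² / 0.11² ≈ 159.3, so 160 per arm against the stated 157.
- One-sided 5%: 126 per arm, which does not fit.

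So 2.5% is the plausible level, and the margin must be 4 absolute percentage points.

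**2. Gross preventive effect implied by the rates.**

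| Component | OMT | Revascularisation without procedural events |
|---|---|---|
| Clinical stroke | 3% | 2% |
| Silent infarct (twice clinical) | 6% | 4% |
| Non-procedural MI | 2% | 2% |
| Composite | 11% | 8% |

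The difference is 3 points. Adding back procedural events gives 8 + (3 × 3) + 1 + 0.1 = 18.1, the plan's 18%. The 3 points are therefore gross; the net assumption is 11 − 18 = −7, in favour of OMT.

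**3. Power for each statement at the planned rates, 157 per arm.** SE = √(0.2455 / 157) = 0.0395.

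- Upper bound below 4 points: Φ(0.11 / 0.0395 − 1.96) = Φ(0.82) = 79.4%.
- Upper bound below 0: Φ(0.07 / 0.0395 − 1.96) = Φ(−0.19) = 42.5%.

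Binomial simulation (400,000 trials) gives 80.2% and 43.2%. In 37.0% of all trials the bound lies below 4 but not below 0. That is 37.0 / 80.2 = 46% of the passes.

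**4. Chance of passing the 4-point test when revascularisation truly has a net benefit.** The formula is Φ((0.04 − d) / SE − 1.96), where d is the true difference, OMT minus revascularisation.

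| True rates (OMT vs revascularisation) | 157 per arm | 1000 per arm |
|---|---|---|
| 11% vs 8% (d = 3 points) | 4.9% | 11.6% |
| 12% vs 11% (d = 1 point) | 13.0% | 55.7% |

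The 1000 per arm corresponds to the 2000 originally calculated for the full trial.

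**5. What a pass requires at this size.** At the planned rates the observed difference must be no more than 4 − 1.96 × 3.95 ≈ −3.75 points, that is, about 3.75 points in favour of OMT. With 11% in both arms it is about 2.9 points in favour of OMT.

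**The case against.** The strongest reply is that the plan credits revascularisation with no net benefit at all. It expects a 7-point disadvantage, and the comparator is the whole procedure including its risk. That stands, and it is why the 3 points must be called gross and derived.

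Second, a pass at this size needs an estimate clearly in favour of OMT, and even a risk-free procedure (11% against 8%) would let OMT pass only about 5% of the time. This also stands. A reader might infer that a pass could never support the hypothesis, or that the test is blind to procedural harm. The figures do not bear that out: the pass rate goes from about 5% with no procedural harm to about 80% at the planned harm. But this protection comes from the width of the interval, not from the margin, and it weakens as the trial grows.

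Third, no section makes the margin a decision rule for the hypothesis. Sample size {14} claims only non-inferiority, Interim analyses {21b} presents the analysis as a check of safety and a guide to design, and the Discussion admits that the trial may neither prove nor refute the hypothesis. This lowers the weight of the point. It does not remove the gap between the stated hypothesis and the only stated criterion.

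Fourth, the full protocol may justify the margin. One can say only that this article gives no reason, not that the margin is unjustified.

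A reader might also infer that OMT would often pass while clearly worse on clinical stroke. That requires holding silent infarcts fixed while clinical stroke rises, against the plan's two-to-one rule. With the rule applied, OMT clinical stroke of 6% against 5% gives composites of 20% and 18%, and a pass rate of about 6.6%.

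**Conclusion.** The point holds in a limited form. The non-inferior region contains the whole gross preventive effect implied by the plan's rates (3 points against 4). A pass excludes only a net benefit of 4 points or more. By itself it does not establish that patients will not benefit, or that surgery causes more events than it prevents. The stated 80% power belongs to the 4-point claim; for the claim against 0 it is about 42–43%.

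This rests on an assumed one-sided 2.5% level, the unpooled normal approximation, the planned rates and the two-to-one silent-infarct rule. The practical risk is small at the planned size. It becomes material if the margin is kept at a size such as 1000 per arm, where a true 1-point benefit of revascularisation would pass about 56% of the time.

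**What to change.** 1. Word a pass as: any net benefit of revascularisation on the 2-year composite is under 4 points. Note beside it the 3-point gross effect implied by the assumed rates.
2. If the 4-point test passes, compare the same one-sided 97.5% bound with 0 in fixed sequence. Reserve the conclusion that patients will not benefit for a bound below 0.
3. State that the 80% power applies to the 4-point claim, and that power is about 43% for the claim against 0.
4. Report the 2-year difference in clinical stroke or periprocedural death with its 95% confidence interval beside the composite, as context and not as a veto.
5. For a re-launch, justify the margin against the preventive effect assumed or observed.

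Items 1 to 4 need changes of wording, one further comparison of a bound already computed, and one further reported interval. Fixed-sequence testing spends no extra alpha, and no more patients or data are needed. The downside is a less favourable stated power for the stronger claim.

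Item 5 may cost patients if it leads to a smaller margin. At the planned rates, and by the formula that gives 160 per arm for 4 points, 3 points would need 193 per arm, 1.5 points 267, and 0 points 394. These figures show the range of cost and do not recommend a margin.

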**Methods:**

Patients are randomised between immediate revascularisation plus OMT versus OMT alone. Suitable patients are those with asymptomatic or symptomatic carotid stenosis ≥50% with an estimated 5-year risk of stroke of <20%, as calculated using the Carotid Artery Risk score. MRI of the brain at baseline and during follow-up will be used as a blinded measure to assess the incidence of silent infarction and haemorrhage, while carotid plaque MRI at baseline will be used to investigate the hypotheses that plaque characteristics determine future stroke risk and help identify a subgroup of patients that will benefit from revascularisation. An initial analysis will be conducted after recruitment of 320 patients with baseline MRI and a minimum of 2 years of follow-up, to provide data to inform the design and sample size for a continuation or re-launch of the study. The primary outcome measure of this initial analysis is the combined 2-year rate of any clinically manifest stroke, new cerebral infarct on MRI, myocardial infarction or periprocedural death.

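### The initial MRI-based analysis is set at 320 patients in the abstract and 360 in the sample size section, with no reconciliation, and 360 falls slightly short of the stated 15% allowance

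*Protocol article*

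**What the plan says.** Sample size {14} derives a 2-year composite rate (clinical stroke, new infarct on MRI, myocardial infarction or periprocedural death) that is "therefore estimated at 11% in the OMT arm alone and 18% in the revascularisation arm". The size that follows from these rates is given as: "314 patients (157 in each arm) provide 80% power to demonstrate that OMT is non-inferior to OMT plus revascularisation". The margin used is 4 percentage points. The same section then adds the allowance for loss: "Allowing for a dropout of 15% of patients missing their 2-year MRI, we plan to recruit 360 patients for the MRI-based analysis".

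The Methods paragraph of the abstract describes the same initial analysis, with the same 2-year composite, but gives another size: "An initial analysis will be conducted after recruitment of 320 patients with baseline MRI and a minimum of 2 years of follow-up".

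Trial status says that randomisation was suspended in October 2020 once enough patients had been recruited for the brain imaging and plaque MRI analyses. It does not give that number. Section {20c} does not foresee imputation of missing data. The article states no significance level.

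**The concern.** Two things look wrong. First, one analysis has two sizes, 320 and 360, and no sentence explains the difference. The abstract counts recruited patients with a baseline MRI and 2 years of follow-up; it does not ask for a 2-year MRI. The Sample size section counts recruits before losing those who miss that scan. It is unclear whether the figures describe different populations, or whether one is out of date.

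Second, 360 is presented as 314 plus a 15% allowance, but taking 15% off 360 does not return 314.

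The initial analysis is meant to assess safety and to inform the design and sample size of a continuation or re-launch. If its size is ambiguous, so is the point at which it falls due, and the stated 80% power is tied to a number of evaluable patients that the recruitment figures may not yield.

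**Working it through.** **Inputs.** From Sample size {14}: event rates 11% (OMT) and 18% (revascularisation), margin 4 points, 157 per arm (314 in total), power 80%, loss 15%, recruitment 360. From the abstract: 320. Allocation is 1:1. Alpha is assumed; one-sided 2.5% is used, with one-sided 5% as the alternative.

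**Step 1: reproduce 314.** With unpooled variance,

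n per arm = (z for 1−α + z for power)² × [p₁(1−p₁) + p₂(1−p₂)] / (margin + p₂ − p₁)²

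- One-sided 2.5%, rates 11% and 18%: (1.960 + 0.842)² = 7.849; variance sum 0.0979 + 0.1476 = 0.2455; distance 0.04 + 0.07 = 0.11. So n = 7.849 × 0.2455 / 0.0121 = 159.2, or 160 per arm (320 in total), 1.9% above the stated 314.
- One-sided 2.5%, with the section's unrounded component sum for revascularisation (15% + 3% + 0.1% = 18.1%): variance sum 0.0979 + 0.1482 = 0.2461; distance 0.111. So n = 7.849 × 0.2461 / 0.01232 = 156.8, or 157 per arm, exactly as stated.
- One-sided 5%, rates 11% and 18%: 126 per arm (252 in total), which does not reproduce 314.

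One-sided 2.5% is therefore the level that fits the stated figure, although the article does not state it.

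**Step 2: the allowance for loss.** If a fraction d is lost, recruits needed = N / (1 − d).

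- 314 / 0.85 = 369.4, so 370.
- 314 × 1.15 = 361.1, which is close to the stated 360.
- 360 × 0.85 = 306, which is 8 below 314.
- 320 × 0.85 = 272, which is 42 below 314, if 320 counts recruits before loss.
- Largest loss that still leaves 314: 1 − 314/360 = 12.8% from 360; 1 − 314/320 = 1.9% from 320.

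These counts do not depend on alpha.

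**Step 3: power at each evaluable number.** Power = Φ(distance / SE − 1.960), with SE = √(variance sum / n per arm).

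| Evaluable | Per arm | Power, 11% v 18% (stated) | Power, 11% v 18.1% (unrounded) |
|---|---|---|---|
| 314 | 157 | 79.4% | about 80% |
| 306 (360 less 15%) | 153 | 78.4% | 79.0% |
| 272 (320 less 15%) | 136 | 73.5% | 74.2% |

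Worked example at 136 per arm with the stated rates: SE = √(0.2455/136) = 0.04249; 0.11/0.04249 − 1.960 = 0.629; Φ = 73.5%.

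**Step 4: can 320 and 360 be reconciled?** If 320 were the number who already have a 2-year MRI, it would exceed 314, but it would need 320/0.85 = 376.5, so 377 recruits, not 360. If it counts recruits, it simply differs from 360. It also equals the uninflated total from the stated rates (2 × 160), so it might be a size before any allowance for loss; the article does not say. Neither reading makes the two figures agree at a 15% loss.

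**The case against.** The strongest reply concerns weight. The shortfall at 360 is trivial: 8 patients and about 1 point of power, well inside the uncertainty of event rates guessed to the nearest percent. That stands, and on its own the slip would be a minor correction. That the planners multiplied by 1.15 instead of dividing by 0.85 is also only an inference, since 314 × 1.15 is 361 rather than 360.

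A reader might infer that the abstract's figure commits the trial to 272 evaluable patients. The text does not establish this. The sentence can be read as counting patients who already have 2 years of follow-up, in which case taking off a further full 15% would partly count the same losses twice. The reference to recruitment favours the reading before loss, but 272 and 73.5% remain conditional on it.

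The evaluable counts are also approximate. A patient with a clinical stroke, a myocardial infarction or a periprocedural death already counts in the composite without a 2-year MRI. Participant timeline {13} allows CT where MRI is contraindicated or unavailable, and {20c} censors patients who stop attending rather than saying they are dropped. The real loss may be below 15%. This narrows the gap but does not show that it closes, and 15% is the plan's own figure.

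Nor is this the trial's main clinical comparison. Outcomes {12} keeps stroke or periprocedural death as the primary outcome of the full trial, and the Discussion accepts that the analysis might not yield sufficient evidence. These points lower the severity; they do not reconcile 320 with 360.

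**Conclusion.** The point holds as a should-fix. The abstract and Sample size {14} give different sizes for one analysis and nothing reconciles them; this is the main finding. Separately, 360 does not deliver the stated 15% allowance: 370 would be needed, and 360 absorbs at most a 12.8% loss.

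The cost in power is about 1 point at 306 evaluable, and about 6 points at 272 if 320 counts recruits before loss, each against 314. These figures rest on an assumed one-sided alpha of 2.5%, the unpooled normal approximation and the full 15% loss. Were one-sided 5% intended, power at 306 and 272 would be 86.5% and 82.7% with the stated rates, but 314 would then not be the 80% figure; the conflict and the counts would be unchanged.

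A reader might go further and conclude that the initial analysis is seriously underpowered at either size. The documents do not support that: the loss at 360 is marginal, and the larger loss depends on a reading of the abstract that the article leaves open.

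**What to change.** - Make the abstract and Sample size {14} give one size for the initial analysis, and say what it counts: recruits, or patients with an ascertained 2-year composite outcome. If 320 and 360 count different things, state how they relate.
- State that 370 is the correct inflation of 314 for a 15% loss. With randomisation suspended this corrects the derivation; it does not ask for more recruitment.
- Restate the power for the number expected to be evaluable, with the significance level beside it. At 15% loss, under the assumptions above, this is about 78% to 79% for 360 recruits and about 74% for 320.
- Do not make completion of both MRI scans a condition for counting patients. It would leave out those whose clinical event already counts in the composite, which sits badly with the intention-to-treat analysis. Nor should the analysis be triggered at 314 patients with both scans: at a 15% loss 360 recruits yield only 306, so the trigger might never be met.

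The cost is wording only. The stated power becomes slightly less favourable, and no extra patients are needed.
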